#### Length of stay (LOS)

LOS is defined as the time (days) between the index emergency operation and the day of discharge.

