#### Permanent ostomy

Permanent ostomy (yes/no) is defined as no stoma reversal within 2 years of the operation, as nearly all reversals are performed within that timeframe [26].

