#### Bowel function

This is the time (days) from operation to the first defecation.

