#### Readmission

This is readmission within 30 days after surgery for any reason (yes/no and reason for readmission).

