### Statistical methods

The findings will be analyzed using SPSS (version 27 or higher) (IBM Corp., Armonk, NY, USA) for Windows. Both intention-to-treat and per-protocol analyses will be performed.

Between-group comparisons of continuous variables will be performed using Student’s *t* test or with the Mann–Whitney *U* test if heterogeneous variances persist. Categorical data will be compared using the *χ*^2^ test or Fisher’s exact test. Long-term survival will be analyzed using Cox regression or Kaplan–Meier’s analysis. Two-tailed *p* values will be reported. *P*-values ≤ 0.05 are considered significant. If data for a certain variable is missing the case will be removed from the analysis in question.

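### Length of stay and time to first defecation give no value to patients who die first, and the removal rule then leaves a survivors-only comparison

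*Protocol article*

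**What the plan says.** Under Length of stay: "LOS is defined as the time (days) between the index emergency operation and the day of discharge". Under Bowel function: "This is the time (days) from operation to the first defecation". Neither definition says what value a patient receives who dies before the event.

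The Statistical methods section fixes two further things. The first is the test: "Between-group comparisons of continuous variables will be performed using Student’s *t* test or with the Mann–Whitney *U* test if heterogeneous variances persist". The second is the missing-data rule: "If data for a certain variable is missing the case will be removed from the analysis in question". No censoring or competing-event method is given for stay or bowel function.

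Two yes/no endpoints are also silent on death. For readmission: "This is readmission within 30 days after surgery for any reason (yes/no and reason for readmission". For ostomy: "Permanent ostomy (yes/no) is defined as no stoma reversal within 2 years of the operation".

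Other endpoints do take account of death. ICU-free days count only days alive, and overall and disease-free survival treat death as an event. Ninety-day mortality is a separate secondary endpoint. The Objectives name shorter stay, less ileus and lower mortality among the expected benefits of laparoscopy.

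**The concern.** Patients who die in hospital are unlikely to be a random sample of those operated on. They tend to be the sicker ones, who would have stayed longest and recovered bowel function latest. Removing them after randomisation improves the average of whichever arm has more deaths, and it departs from the intention-to-treat analysis that the same section promises.

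The trial itself expects the number removed to differ between arms. The two outcomes affected correspond to benefits that it names in advance. If laparoscopy does save lives, its survivors include frailer patients whose counterparts in the open arm have been dropped, so a real gain in stay or bowel recovery is understated. If laparoscopy costs lives, the same rule makes it look better on these outcomes.

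**Working it through.** The protocol states no figure on this point, so there is none to reproduce. The check has two parts: how each definition treats a death, and how large the effect could be.

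**How each definition treats a death**

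| Endpoint | Patient who dies first | Consequence |
|---|---|---|
| Length of stay | No day of discharge; value missing; removed | Survivors only |
| First defecation | No event; value missing; removed | Survivors only |
| GIQLI at 90 days | No questionnaire; removed | Survivors only |
| Readmission | Cannot be readmitted | Counted silently as 'no', or undefined |
| Permanent ostomy | Died with stoma, no reversal | Literally meets the definition |

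**Inputs.** From the protocol: the definitions, the removal rule and 96 patients per group. Everything else is assumed, because the protocol gives no mortality, stay, readmission or stoma rates. Mortality in the two arms was taken as 5% v 10%, 5% v 15% and 10% v 20%.

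**Length of stay.** Both arms have the same underlying stay: log stay = ln 8 + 0.5u + 0.3e, with u (frailty) and e standard normal. The true mean is 8 × exp((0.25 + 0.09)/2) = 8 × exp(0.17) = 9.48 days in each arm. Death follows logit(p) = c + 1.5u, with c set to give the stated mortality. With 400,000 simulated patients per arm (lower-mortality arm first):

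| Mortality | Mean, deaths removed | Median, deaths removed | Mean, day of death taken as discharge | 75th percentile, deaths ranked worst |
|---|---|---|---|---|
| 5% v 10% | 9.07 v 8.80 | 7.78 v 7.59 | 8.97 v 8.62 | 12.23 v 12.93 |
| 5% v 15% | 9.09 v 8.50 | 7.78 v 7.38 | 8.99 v 8.26 | 12.27 v 14.03 |
| 10% v 20% | 8.77 v 8.26 | 7.58 v 7.20 | 8.59 v 7.98 | 12.92 v 16.29 |

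With deaths removed, the arm with more deaths looks better by 0.27, 0.59 and 0.51 day in the mean. The medians shift the same way, so moving from the t test to Mann–Whitney does not cure it. Entering day of death as discharge does not cure it either. Ranking death worst reverses the direction.

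**Dependence on the frailty link.** At 5% v 15%, a model with a true mean of 11.0 days and a correlation near 0.6 between latent stay and latent death gives 10.4 v 9.6 days, a gap of 0.8. At a correlation of 0.4 the gap is about 0.46. Further runs at the same mortality gave about 0.1 to 0.6 day.

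**Against sampling error.** In the tabulated model the SD is 9.48 × √(exp(0.34) − 1) = 9.48 × 0.636 = 6.03 days. With 96 per arm, SE = 6.03 × √(2/96) = 0.87 day. A shift of 0.27 to 0.59 day is therefore about 0.3 to 0.7 SE.

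**First defecation and GIQLI.** The mechanism is the same; no size was computed. First defecation usually comes before discharge, so fewer deaths should precede it.

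**Permanent ostomy.** Assume 50% receive a stoma and 60% of survivors have it reversed. Read literally, the rate at mortality m is (1 − m) × 0.5 × 0.4 + m × 0.5. This gives 21.5% at 5%, 23.0% at 10%, 24.5% at 15% and 26.0% at 20%. The arm with more deaths looks worse, by 1.5 to 3 points.

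**Readmission.** Assume 15% of survivors are readmitted and deaths count as 'no'. The rate is 0.15 × (1 − m): 14.25%, 13.5%, 12.75% and 12.0% at the same four mortalities. The arm with more deaths looks better by 0.75 to 1.5 points.

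**The case against.** **Article brevity.** This is a condensed article, and the coding of in-hospital deaths for secondary outcomes is often left to a fuller document. No sentence says that deaths are excluded; that follows from the definitions together with the removal rule. This would be a good answer if the article were silent, but it fixes both the endpoints and the removal rule, and applying them as written gives the survivors-only result.

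**Size.** The distortion is under one standard error at this sample size, the endpoints are secondary, and mortality is reported beside them. A mortality gap large enough to matter would probably be noticed there. This stands, and it limits the weight of the point. Reporting mortality separately does not, however, correct the comparison of stay or bowel function.

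**Direction.** Under the trial's own hypothesis the bias runs against laparoscopy. That also stands. It makes a false claim for laparoscopy less likely, but a true benefit harder to see.

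**Two stronger readings.** A reader might infer that all these endpoints flatter the arm with more deaths. The ostomy definition does not support that: taken literally, it penalises that arm.

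A reader might also infer that counting readmission from surgery is an error, because earlier discharge gives more days at risk. With a hazard of 12% per 20 days, h = −ln(0.88)/20 = 0.00639 per day. Stays of 12 v 7 days then give 1 − exp(−18h) = 10.9% v 1 − exp(−23h) = 13.7%. Those stays are assumed and no deaths enter the calculation; with 12 v 10 days it is 10.9% v 12.0%. The window matches the 30-day postoperative window used for the primary endpoint and for reoperation. Counting from discharge among those discharged alive would itself condition on survival. The window is a defensible choice; only the silent 'no' needs attention.

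**Conclusion.** The point holds for length of stay and time to first defecation, and in the same way for GIQLI at 90 days: the stated rules compare survivors only in a trial that expects mortality to differ by arm. For mean stay the distortion is about 0.3–0.6 day in favour of the higher-mortality arm. This assumes mortality of 5–10% v 10–20%, identical underlying stays, and that patients who die would have stayed longer. It approaches 0.8 day only with longer stays and a strong link between stay and death, and can be as small as 0.1 day with a weak one. None of these rates comes from the protocol.

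Permanent ostomy and readmission need clearer reporting of deaths, but they do not share one direction of bias. The primary endpoint is not affected. The change should be made, but the trial's main conclusion does not depend on it.

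**What to change.** - **Removal rule:** state that death is not missing data and is exempt from removal.
- **Length of stay and first defecation:** include every randomised patient, rank death before the event as worst, and compare by a rank test. Give survivors-only summaries as description.
- **GIQLI:** add a sensitivity analysis with deaths before the assessment ranked worst.
- **Permanent ostomy:** at 2 years, report alive with ostomy, alive without ostomy and dead as separate categories.
- **Readmission:** keep the 30-day postoperative window. Report death before discharge and still in hospital at day 30 beside it, not as 'no'.

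The cost is definition and analysis wording and slightly more analysis work, and length of stay is no longer summarised by a simple mean alone. Nearly all the data are already collected: stay and first bowel movement are in the post-intervention data, and ICU-free days already require survival to day 30. One small addition may be needed. Table 2 schedules mortality only at 90 days and survival at 1, 3 and 5 years for oncologic patients, so vital status should be recorded for everyone at the 2-year ostomy check. Worst-rank is one of several accepted ways to handle death; what matters is that one is fixed before outcomes are compared by arm.

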### Objectives

The objective of this study is to evaluate whether patients benefit from the laparoscopic approach in emergency colorectal surgery, whether benign or malignant disease.

Our hypothesis is that the same beneficial effects of laparoscopy seen in elective surgery and in other entities needing emergency surgery will also apply to emergency colorectal surgery. These benefits are lower overall postoperative morbidity, shorter in-hospital stay, less postoperative ileus, less postoperative pain, fewer wound complications, and lower risk of mortality.

For oncologic patients, our hypothesis is that the laparoscopic approach is superior to the open approach, partly because of the faster recovery associated with greater access to oncologic treatment and partly because in laparoscopy the intra-operative circumstances need to be optimized to mimic the elective situation, leading to good visualization and a standardized approach.

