### Eligibility criteria

#### Inclusion criteria

The patient has a condition necessitating emergency colorectal resection. We define the timeframe for emergency colorectal resection to be within 0–48 h from the decision to proceed with surgery.Age 18 years or olderThe patient is competent to give their consentSigned informed consent

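### Length of stay has no valid value for patients who die in hospital, so the arm with more deaths can look faster

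*Protocol article*

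**What the plan says.** All of this comes from the protocol article.

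- **Length of stay (LOS)**, a secondary endpoint: "LOS is defined as the time (days) between the index emergency operation and the day of discharge". The section does not say what value a patient who dies before discharge receives.
- **Bowel function**, also secondary: "This is the time (days) from operation to the first defecation". It has no rule for death before the event either.
- **Statistical methods**: "If data for a certain variable is missing the case will be removed from the analysis in question". For continuous variables the section names only the t test ("Between-group comparisons of continuous variables will be performed using Student’s" t test) or the Mann-Whitney U test. It also promises: "Both intention-to-treat and per-protocol analyses will be performed".
- **Objectives**: "These benefits are lower overall postoperative morbidity, shorter in-hospital stay, less postoperative ileus". Lower mortality is on the same list of expected benefits.
- **Intensive care unit (ICU)-free days**: only days on which the patient is alive up to day 30 count, so death is built into that endpoint.
- **Ninety-day mortality**: a separate yes/no endpoint.

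**The concern.** Discharge is an event that death prevents. A stay that ends in death is not an unobserved number that could have been collected or imputed, and the plan gives no other value for it. That leaves two ways of filling the field.

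1. The field is left empty and the complete-case rule removes the patient. LOS then compares only those who left hospital alive, a group defined by something that happened after randomisation. If patients near death would otherwise have had long stays, the arm that saves them gains long stays and the other arm loses them.
2. The day of death is entered as the day of discharge. An early death then scores as a quick recovery.

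Both routes pull the same way: the arm with more deaths looks faster. The Objectives hypothesise lower mortality and shorter stay for the same intervention, so if the first is true, the test of the second is distorted by it. Removing deaths also sits badly with the promised intention-to-treat analysis. The Background describes emergency resection as carrying a higher risk of in-hospital death than elective surgery, so such patients should be expected here.

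**Working it through.** **Inputs.** The document gives no LOS figure to reproduce, and no in-hospital mortality or LOS by arm. The only figure taken from it is the planned size, 96 per arm (Sample size). Everything else below is assumed.

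**Patients affected.** With assumed in-hospital mortality of 5% to 20%: 96 × 0.05 = 4.8 and 96 × 0.20 = 19.2, so about 5 to 19 patients per arm would have no valid LOS.

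**Hand example, deaths removed.** Assume the usual stay is 10 days and that patients who die in one arm but are saved in the other stay 25 days when saved. Survivors in the arm with more deaths average 10.0 days. In the arm with fewer deaths:

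- 5% v 10% mortality: (0.90 × 10 + 0.05 × 25) / 0.95 = 10.79 days
- 3% v 6%: (0.94 × 10 + 0.03 × 25) / 0.97 = 10.46 days
- 5% v 15%: (0.85 × 10 + 0.10 × 25) / 0.95 = 11.58 days

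The arm that saves patients looks 0.8, 0.5 and 1.6 days worse. These sizes depend heavily on the assumed 25 days; the example shows the mechanism and direction.

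**Hand example, death entered as discharge.** Assume survivors stay 10 days in both arms and deaths occur on day 5. With 5% mortality: 0.95 × 10 + 0.05 × 5 = 9.75 days. With 10%: 0.90 × 10 + 0.10 × 5 = 9.50 days. The arm with more deaths looks 0.25 day better.

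**Simulation.** 400,000 patients per arm were drawn. Potential LOS was lognormal with median 9 days and log-SD 0.6, identical in both arms. Death was more likely in sicker patients, who would also have stayed longer. Time to death was exponential with mean 6 days. Only mortality differs between arms. Entries are arm B minus arm A, in days; a negative value means arm B looks faster.

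| Mortality A v B | Deaths removed: mean / median | Death = discharge: mean / median | Deaths ranked worst: median |
|---|---|---|---|
| 5% v 5% | +0.03 / +0.02 | +0.03 / +0.02 | +0.02 |
| 5% v 10% | −0.26 / −0.19 | −0.46 / −0.36 | +0.19 |
| 5% v 15% | −0.47 / −0.33 | −0.85 / −0.65 | +0.49 |
| 10% v 15% | −0.24 / −0.19 | −0.41 / −0.33 | +0.24 |
| 10% v 20% | −0.40 / −0.30 | −0.74 / −0.60 | +0.65 |

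With unequal mortality, the arm with more deaths looks faster by 0.24-0.47 day in the mean if deaths are removed, and by 0.41-0.85 day if death counts as discharge. Ranking deaths worst reverses the sign in every such row. With equal mortality nothing of note remains.

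**Set against sampling error.** The assumed lognormal has variance 81 × e^0.36 × (e^0.36 − 1) ≈ 50.3, so SD ≈ 7.1 days. With 96 per arm, the standard error of a mean difference is about 7.1 × √(2/96) ≈ 1.0 day. The bias is therefore about a quarter to a half of one standard error when deaths are removed, and about 0.4 to 0.8 when death counts as discharge.

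**The case against.** **Silence, not error.** The article condenses a fuller plan, and the handling of death in a secondary endpoint is often left to the analysis plan. The deletion rule speaks of missing data and does not mention death. It is true that the article does not say outright which of the two routes applies. But it does fix the endpoint's end, the deletion rule and the tests, and following them leads to one unsound treatment or the other. The ICU-free days definition shows that death can be built into an endpoint of this kind.

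**Small, and visible elsewhere.** The bias is modest, rests on assumed inputs and vanishes with equal mortality. If laparoscopy does lower mortality, the bias runs against it and is conservative for the trial's claim. Mortality is reported separately, and the primary endpoint is untouched. All of this stands, and it limits the weight of the point. It does not make the LOS comparison valid: a reader who sees a mortality imbalance cannot undo its effect on the LOS p-value, and if laparoscopy had more deaths the bias would favour it.

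**A stronger reading that the document does not support.** Patients are randomised before surgery, and surgery may take place "within 0–48 h from the decision to proceed with surgery". A reader might infer that the clock should start at randomisation because a longer wait in one arm would shorten its LOS. It would not: time from operation to discharge is unaffected by the wait before it. Nothing in the document suggests that waits differ by arm. Most other short-term outcomes are also anchored to surgery, and a randomisation date is not among the listed data items. Operation to discharge is a coherent postoperative measure. What remains is a matter of labelling, since the Objectives speak of "shorter in-hospital stay".

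**Conclusion.** The point holds for in-hospital death. As written, the plan either drops such patients from LOS or lets an early death score as a short stay, and both tend to favour the arm with more deaths. The size is modest: roughly 0.2-0.5 day in the mean if deaths are removed and 0.4-0.85 day if death counts as discharge, for assumed mortality of 5-10% v 10-20%, and about zero if mortality is equal.

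The direction rests on two assumptions: that patients who die would otherwise have stayed longer than average, and, for the second route, that deaths come early relative to the usual stay. The same gap affects time to first defecation; no size was worked out for it.

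This deserves correction because LOS carries a named hypothesis. It does not threaten the primary endpoint and does not require the clock to start at randomisation.

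**What to change.** 1. In the LOS section, define the outcome as postoperative time from the index operation to discharge alive, and call it postoperative stay.
2. Keep in-hospital deaths in the intention-to-treat analysis by one method chosen in advance: rank them worst in a Mann-Whitney test, fixed as the test for this endpoint; or compare the cumulative incidence of live discharge with death as a competing event.
3. In Statistical methods, state that death before the event is not missing data and is exempt from the deletion rule.
4. Treat death before first defecation in the same way.
5. Report LOS among survivors as a description only, without using it to test the hypothesis.

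**Cost.** Wording in three sections and slightly more analysis. LOS and mortality are already collected. Ranking needs only the fact of death before discharge; the competing-event analysis also needs its date, which ICU-free days already require up to day 30. The LOS summary becomes less simple, and a worst-rank result reflects survival and stay together, so it should be read beside the mortality result. The article describes recruitment as still open, so the change can be made before analysis.

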#### Permanent ostomy

Permanent ostomy (yes/no) is defined as no stoma reversal within 2 years of the operation, as nearly all reversals are performed within that timeframe [26].

#### Reoperation risk

This is reoperation within 30 days after primary intervention (yes/no) and the reason for reoperation. Only operations that are due to a (suspected) complication and directly related to the primary operation are considered as a reoperation.

#### Bowel function

This is the time (days) from operation to the first defecation.

#### Readmission

This is readmission within 30 days after surgery for any reason (yes/no and reason for readmission).

#### Quality of life (QoL)

QoL is measured by the GIQLI health survey [27] 90 days after surgery.

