#### Exclusion criteria

The patient’s condition is due to traumaSimultaneous acute pancreatitisThe need for resection is due to a complication from a previous procedure, i.e., reoperationSimultaneous ruptured aortic aneurysm or ruptured aortic aneurysm as the underlying cause of the need for surgery

All patients arriving in the emergency room and diagnosed with a condition requiring emergency colorectal resection will be considered for inclusion. After receiving proper information on the possible advantages and disadvantages of the intervention, and after voluntarily signing the informed consent form, the subjects will be enrolled in the trial. The written consent will be obtained by a member of the research group and a copy given to the patient. After enrolment, the patient will be randomized for either open or laparoscopic surgery. The procedure will be carried out or closely supervised by a specialist in gastrointestinal surgery experienced in colorectal resections. Patients considered but not meeting the inclusion criteria and patients with at least one exclusion criterion will not be enrolled. These patients and the reasons for their exclusion will be documented. Postoperative care and follow-up will follow normal praxis and the case report form will be completed. Ninety days after surgery, patients will be requested to fill in the Gastrointestinal Quality of Life Index (GIQLI) questionnaire, which is the only deviation from normal follow-up. The GIQLI questionnaire will be sent by post at no cost to the patient. Once enrolled, patients will not be required to make any further visits to the hospital or to undergo any radiation or medical procedures. The follow-up for oncology patients will also be arranged according to the normal follow-up schedule.

If at any point the allocated type of intervention needs to be modified or even discontinued because of patient safety or for any other reason, the circumstances and reasons will be carefully documented and the patient will be informed. For example, if the patient’s condition changes, making the patient unfit for surgery, the patient will normally be excluded. In the event of conversion during the operation, the circumstances will be carefully documented but the patient will still be able to participate.

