#### Ninety-day mortality

Ninety-day mortality is death for any reason within 90 days of surgery (yes/no).

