#### Intensive care unit (ICU)-free days

ICU-free days are defined as the number of days during which the patient is alive up to 30 days postoperatively minus days spent in the ICU (range 0–30).

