### Sample size

Sample size calculations will be based on previous studies, which report 48.3% 30-day postoperative morbidity after open surgery and 27.8% after laparoscopy [22]. The aim of the study is to show that postoperative morbidity is lower after laparoscopic surgery. Assuming *α* = 0.05 and a (?) power = 80, 87 patients are needed for both groups. The effect size is 0.54. Assuming a 10% patient drop-out rate during the 30-day follow-up period, a total of 192 patients, i.e., 96 in each group, is needed.

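### The missing-case rule makes no exception for death, so the 90-day GIQLI comparison is confined to survivors and can be modestly biased if mortality differs by arm

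*Protocol article*

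**What the plan says.** All of this is in the Protocol article.

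- **Endpoint.** Under Quality of life (QoL), a secondary endpoint: "QoL is measured by the GIQLI health survey [27] 90 days after surgery". No value or rule is attached to death.
- **Collection.** The text under Exclusion criteria adds: "The GIQLI questionnaire will be sent by post at no cost to the patient". Table 2 places GIQLI and mortality in the same 90 (+60) day column.
- **Missing data.** Statistical methods has one rule for every variable: "If data for a certain variable is missing the case will be removed from the analysis in question". The same section promises both intention-to-treat and per-protocol analyses. Continuous variables are compared by t test, "or with the Mann–Whitney *U* test if heterogeneous variances persist".
- **Mortality.** All-cause death within 90 days of surgery is a separate secondary endpoint. Among the expected benefits of laparoscopy, the Objectives list "fewer wound complications, and lower risk of mortality".
- **Contrast.** ICU-free days do take account of death, because they are defined as "the number of days during which the patient is alive up to 30 days postoperatively minus days spent in the ICU". GIQLI has no counterpart to this.

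**The concern.** A questionnaire that a living patient did not return is missing: a score existed and was not observed. A patient who died before day 90 has no score to observe. The general rule treats the two alike and removes both.

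What remains is a test among people who survived and responded. Survival is an outcome of the randomised treatment, so randomisation no longer protects the comparison, even in the analysis called intention-to-treat. If laparoscopy prevents deaths, and the patients it saves have poorer quality of life than the rest, those patients enter only the laparoscopic mean and lower it. If laparoscopy caused extra deaths, which the Discussion does not rule out when it mentions unrecognised risks, the same rule would flatter it. In either case an apparent difference in GIQLI can arise with no change in any individual's quality of life.

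**Working it through.** **The plan's own figure.** No figure is stated for QoL. The only planned size is for 30-day morbidity, "48.3% 30-day postoperative morbidity after open surgery and 27.8% after laparoscopy". The pooled two-proportion formula, two-sided 0.05 and 80% power, gives [1.960 × √(2 × 0.3805 × 0.6195) + 0.842 × √(0.483 × 0.517 + 0.278 × 0.722)]² / 0.205² = 86.9, so 87 per group as stated. I use the enrolled size of 96 per group below; the figure has no other bearing on this point.

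**Assumptions, none of them in the article.** Ninety-day mortality (open versus laparoscopic) of 5% vs 3%, 10% vs 5%, 15% vs 8% or 20% vs 10%. GIQLI SD 20. The approach changes no patient's GIQLI. Patients saved by laparoscopy score g points below the other survivors, with g from 10 to 35.

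**Step 1: who is removed.** 96 × mortality gives about 5 to 19 open patients (96 × 0.05 = 4.8; 96 × 0.20 = 19.2) and 3 to 10 laparoscopic patients (96 × 0.03 = 2.9; 96 × 0.10 = 9.6).

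**Step 2: bias of the survivor mean.** Saved patients make up (m_open − m_lap)/(1 − m_lap) of laparoscopic survivors, so

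laparoscopic minus open = −g × (m_open − m_lap)/(1 − m_lap).

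For 15% vs 8% and g = 35: 0.07/0.92 × 35 = 2.66 points against laparoscopy.

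**Step 3: compare with sampling error.** SE = 20 × √(1/n_open + 1/n_lap) among survivors. For 15% vs 8%: 20 × √(1/81.6 + 1/88.3) = 3.07.

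| Mortality | g = 10 | g = 20 | g = 30 | g = 35 | SE | Largest bias / SE |
|---|---|---|---|---|---|---|
| 5% vs 3% | −0.21 | −0.41 | −0.62 | −0.72 | 2.95 | 0.24 |
| 10% vs 5% | −0.53 | −1.05 | −1.58 | −1.84 | 3.00 | 0.61 |
| 15% vs 8% | −0.76 | −1.52 | −2.28 | −2.66 | 3.07 | 0.87 |
| 20% vs 10% | −1.11 | −2.22 | −3.33 | −3.89 | 3.14 | 1.24 |

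With no true QoL effect, the chance of a two-sided p below 0.05 is P(Z > 1.96 − r) + P(Z < −1.96 − r), where r is bias/SE. This is 6% at r = 0.24, 14% at r = 0.87 and 24% at r = 1.24, instead of 5%. Survivors who do not respond would make the SE larger and r smaller.

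**Step 4: what ranking death lowest does.** At 15% vs 8% and g = 35, the chance that a random laparoscopic survivor scores above a random open survivor is 0.0761 × Φ(−35/28.28) + 0.9239 × 0.5 = 0.470. With all randomised patients and death lowest it is 0.92 × 0.15 + 0.92 × 0.85 × 0.470 + 0.5 × 0.08 × 0.15 = 0.512. For g = 20 the pair is 0.480 and about 0.52. The standard error of the second index at 96 per arm is about √(193/(12 × 96 × 96)) = 0.042, so 0.512 and 0.52 both lie within half a standard error of 0.5.

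**The case against.** Four things can fairly be said against the point.

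- **The exclusion of deaths is an inference.** A reader might take the article to have decided to exclude deaths from QoL. It has not: the missing-case sentence names neither death nor GIQLI, and an analysis plan may treat death separately. This limits the wording but does not remove the point. The rule that is stated covers every variable and has no exception.
- **Mortality is reported anyway.** Ninety-day death is its own endpoint, so a reader will have both results. That stands, and GIQLI among survivors is a legitimate descriptive quantity. What is lacking is a label saying that the test is conditional on survival, and a commitment to show the two together.
- **Ranking death lowest is not simply the correct answer.** A reader might infer from Step 4 that the survivor analysis has the wrong sign and the ranked one the right sign. In that scenario nobody's quality of life changes, so the ranked advantage comes entirely from mortality, which is already counted elsewhere. Both indices are also too close to 0.5 for this trial to tell apart from no difference. Ranking deaths also leaves open what to do with survivors who do not respond.
- **The size is assumed.** The trial enrols only patients able to consent, so mortality could be at the low end, where the bias is well under one point. It vanishes if mortality does not differ by arm, or if saved patients score like everyone else.

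**Conclusion.** The point holds as a qualified one. The stated deletion rule, applied to the stated endpoint, produces a survivors-only and therefore non-randomised comparison in a trial that itself expects mortality to differ by arm. The direction is against whichever arm has fewer deaths, provided that the extra survivors score lower.

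In most of the assumed scenarios the bias is below one standard error; it passes that only at 20% vs 10% with saved patients scoring 30 or more points lower. It can therefore hide or tilt a small GIQLI difference, and would usually not reach significance without help from chance. The stronger claim, that the QoL conclusion will be reversed, is not supported, because the article gives no mortality rate, GIQLI mean or SD. Only a secondary endpoint is touched; the primary analysis and the sample size are not.

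**What to change.** Change the Quality of life (QoL) and Statistical methods sections as follows.

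1. State that death is not missing data for GIQLI: deaths are exempt from the missing-case rule, no score is imputed for them, and they are counted by arm separately from non-response.
2. Label the GIQLI comparison in survivors as conditional on survival, and show it beside 90-day mortality by arm.
3. Add a Mann–Whitney comparison in which death by day 90 ranks below every GIQLI score, with a sentence saying that this composite also reflects mortality.
4. State that surviving non-responders remain missing and are reported by arm. Because Table 2 allows 90 (+60) days, also say how a death after day 90 but before the form is returned is counted.

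**Cost.** A few sentences and one extra analysis. No new data are needed, since mortality and GIQLI are already collected in the same Table 2 column, and the test is already named. The downside is that the ranked result is not in GIQLI points and overlaps with the mortality endpoint, so it should stand beside the survivor result and not replace it.
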